## Abstract

**Objective:**

Mental health complaints are prevalent among people with epilepsy, yet there are major barriers that prevent access to psychological care, including high out‐of‐pocket costs and a lack of accessible specialized services. The purpose of the current study is to examine the comparative efficacy, acceptability, cost‐effectiveness, and long‐term outcomes of a digital psychological intervention when delivered under two models of care (i.e., guided vs. unguided) in supporting the mental health and functioning of adults with epilepsy.

**Method:**

Approximately 375 participants across Australia will be enrolled. Eligible participants will have a confirmed diagnosis of epilepsy, experience difficulties with their emotional health, be at least 18 years of age, and live in Australia. Participants will be randomized (2:2:1) to receive the Wellbeing Neuro Course, a 10‐week internet‐delivered program, with (i.e., guided) or without guidance by a mental health clinician (i.e., unguided), or be allocated to a treatment‐as‐usual waiting‐list control group. Participants will complete online questionnaires at pre‐, post‐treatment, and 3‐ and 12‐month follow‐up and consent to have their data linked to their medical records to capture healthcare system resource use and costs.

**Analysis:**

Primary outcome measures will be symptoms of depression and anxiety. A cost‐utility analysis will be undertaken using the Australian healthcare system perspective and according to current economic evaluation guidelines. Resource use and costs to the healthcare system during the study period will be captured via data linkage to relevant administrative datasets in Australia.

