### Study design

2.2

A three‐group CONSORT‐R Compliant RCT design will be employed. Participants will be randomized to:
Immediate guided treatment group (*n* = 150), who receive access to the Wellbeing Neuro Course with clinician support.Immediate unguided treatment group (*n* = 150), who receive access to the Wellbeing Neuro Course without clinician support.TAU‐WLC group (*n* = 75), who will crossover to receive access to the Wellbeing Neuro Course at the 3‐month follow‐up period for groups 1 and 2 (approx. 6 months from baseline). They will have the choice of receiving clinician support or doing the course unguided.

A substudy involving a brief survey of the participants' referring or primary epilepsy health professionals' views on the usefulness of the intervention and care pathway will also be conducted.

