### Measures

2.7

A timeline of administration for the measures used is summarized in Table 1.

**TABLE 1 epi412913-tbl-0001:** Timeline for administration of measures.

Measure	Assessment	Pre‐treatment (baseline)	Weekly during treatment	Post‐treatment (10‐week treatment)	3‐month follow‐up	12‐month follow‐up
Participant measure						
Demographics	X					
QuickSCID‐5	X					
Condition details	X					
PHQ‐9	X	X		X	X	X
PHQ‐2			X			
GAD‐7	X	X		X	X	X
GAD‐2			X			
WHODAS 2.0	X	X		X	X	X
NDDIE	X	X		X	X	X
NDDIE‐suicide item			X			
BrEASI	X	X		X	X	X
NeurQol_Cognitive function		X		X	X	X
Seizure frequency	X	X	X	X	X	X
CCSQ		X		X	X	X
TSQ				X		
ReQOL‐10		X		X	X	
EQ‐5D‐5L		X		X	X	
Use of care services (purpose‐built based on the iMTA TIC‐P)		X		X	X	

Abbreviations: BrEASI, Brief Epilepsy Anxiety Instrument; CCSQ, Compensatory Cognitive Strategies Questionnaire; GAD‐7, Generalized Anxiety Disorder – 7; iMTA, Institute for Medical Technology Assessment; NDDI‐E, Neurological Depressive Disorder Inventory‐Epilepsy; PHQ‐9, Patient Health Questionnaire‐9; QuickSCID‐5, Quick Structured Clinical Interview for DSM‐5; ReQOL‐10, Recovering Quality of Life 10‐item; TIC‐P, Treatment Inventory of Costs in Patients with Psychiatric Disorders; TSQ, Treatment Satisfaction Questionnaire.

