### Health economic evaluation

3.5

As with similar programs,^29^ the costs associated with treatment outside the procedures are expected to be skewed to the right, with many participants potentially having zero or little healthcare costs while a small proportion of others having large healthcare costs. Heteroskedasticity within the data is also a potential problem. We will therefore employ a generalized linear model (GLM) to deal with skewness and heteroskedasticity.^48^

Healthcare resource use data for participants in each trial arm will be obtained from the Australian Institute of Health and Welfare (AIHW). Differences in healthcare costs will be compared to differences in health‐related quality of life measured using the ReQoL.^40^ Cost‐effectiveness will be reported as an incremental cost‐effectiveness ratio (ICER), which will be compared to an implicit threshold derived from recommendations made by the Australian Government's Pharmaceutical Benefits Advisory Committee.^49^ Uncertainty around the ICER will be explored using deterministic and probabilistic sensitivity analyses, which will be reported on a cost‐effectiveness acceptability curve.

We will assess the potential impact on government budgets from scaling up the most cost‐effective intervention within Australia. This will include estimating how many patients could benefit from the intervention and potential changes to the use of other services. We will develop a Health Economics Analysis Plan to guide the economic evaluation and align our modeling approach with the ISPOR Good Research Practices for cost‐effectiveness analysis.^50^ Reporting would adhere to the Consolidated Health Economic Evaluation Reporting Standards 2022^51^ and evaluation reporting methods.

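### ReQoL-10 and self-reported service use stop at the 3-month follow-up, so cost-utility of guided versus unguided care beyond about 6 months could only be extrapolated

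*Protocol article*

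**What the plan says.** **Cost window.** The abstract's analysis paragraph states: "Resource use and costs to the healthcare system during the study period will be captured via data linkage". Neither it nor Section 3.5 says when that period ends. The abstract's method paragraph gives the length of follow-up: "Participants will complete online questionnaires at pre‐, post‐treatment, and 3‐ and 12‐month follow‐up".

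**How costs and outcomes are combined.** Section 3.5: "Differences in healthcare costs will be compared to differences in health‐related quality of life measured using the ReQoL". The result is to be an incremental cost-effectiveness ratio (ICER). No time horizon is given, and detail is left to a separate document: "We will develop a Health Economics Analysis Plan to guide the economic evaluation and align our modeling approach".

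**Measurement schedule.** In Table 1 (Section 2.7) the care-use row reads "Use of care services (purpose‐built based on the iMTA TIC‐P) X X X". By column position the three marks are pre-treatment, post-treatment and 3-month follow-up. The ReQoL-10 and EQ-5D-5L rows have the same pattern. PHQ-9, GAD-7, WHODAS 2.0, NDDI-E, BrEASI, Neuro-QoL and CCSQ all have a further mark at 12 months.

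**Crossover.** Section 2.2 lets the waitlist start the course at the 3-month follow-up of the active arms, "approx. 6 months from baseline". No crossover is described between the guided and unguided arms.

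**Hypothesis.** The third hypothesis in the Introduction expects both active arms to be cost-effective against the waitlist, and unguided to be more cost-effective than guided.

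**The concern.** The objective in the abstract names both cost-effectiveness and long-term outcomes of the two models of care, and Section 3.5 goes on to a budget-impact assessment of scaling up the most cost-effective one. Guided versus unguided is the only randomised contrast that survives to 12 months. Yet the measure that supplies the effect side of the ICER is not taken at that visit, even though participants are already completing an online survey then. The care-use form, which Section 2.7.5 describes as covering services that linkage misses, stops at the same point. After the 3-month visit only linked costs would be observed.

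Two things are at stake. An ICER for guided versus unguided beyond about 6 months would rest on assumed rather than observed quality of life, and an analysis plan written later cannot recover data that were not collected. Also, because the cost window is left open, costs could be counted over a longer interval than utilities, or waitlist costs counted after the waitlist has been treated.

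**Working it through.** **Step 1. Is the blank 12-month cell real?** Set the Table 1 rows side by side, by column:

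| Row | Pre | Post | 3-month | 12-month |
|---|---|---|---|---|
| CCSQ | X | X | X | X |
| ReQoL-10 | X | X | X | – |
| EQ-5D-5L | X | X | X | – |
| Use of care services | X | X | X | – |

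CCSQ starts at the same column and has one more mark, so the missing entry is the 12-month one.

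**Step 2. Timeline.** Inputs: a 10-week course (Section 2.6), visits at 3 and 12 months (Table 1), and crossover at about 6 months (Section 2.2). The article does not say outright where the follow-up visits are counted from, so both readings of the 12-month visit are shown.

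- End of course: 10 × 7 / 30.4375 = 2.3 months.
- 3-month visit, counted from end of course: 2.3 + 3 = 5.3 months, roughly in line with the stated 6 months.
- 12-month visit, counted from end of course: 2.3 + 12 = 14.3 months.
- 12-month visit, counted from baseline: 12 months.

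**Step 3. Time without observed utility.**

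- Counted from end of course: 14.3 − 5.3 = 9.0 months; 9.0 / 14.3 = 63%.
- Counted from baseline: 12 − 5.3 = 6.7 months (56%), or 12 − 6 = 6 months (50%).

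**Step 4. Longest cost window the wording permits, relative to the utility window.**

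- 14.3 / 5.3 = 2.7
- 12 / 5.3 = 2.3
- 12 / 6 = 2.0

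If linked costs are cut at the 3-month visit, the ratio is 1 and there is no mismatch.

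**Step 5. Which contrast is affected?**

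- Active arms versus waitlist: the randomised comparison with usual care ends at crossover, the same visit at which utilities end. The schedule fits.
- Guided versus unguided: the comparison stays randomised to 12 months, with no utility or self-reported service use after the 3-month visit. The schedule falls short here.

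**The case against.** The strongest reply is that nothing in the article commits the trial to a mismatched analysis. The study period is undefined, Section 3.5 sets no cost window, and linked claims can be restricted to the interval in which ReQoL-10 is measured. Horizon and cost window are normal content for the Health Economics Analysis Plan that Section 3.5 promises. The 3-month stop is also the last point at which all three randomised arms can be compared. The objective lists cost-effectiveness and long-term outcomes as separate items, and no 12-month ICER is promised. EQ-5D-5L is there only for validation, and the care-use form only supplements linkage.

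Most of this stands, and it rules out three stronger readings that a reader might infer:

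- **That the ICER will mix horizons.** The text permits this but does not plan it.
- **That waitlist costs after crossover contaminate the result.** No section proposes to use them as usual-care costs.
- **That the ICER is overstated 2.7-fold.** That needs costs counted to 14.3 months, a constant utility difference, and cost differences that keep accruing evenly. None of these is stated. Clinician time falls within the 10-week course, so part of the guided–unguided cost difference comes early. If later healthcare use fell in one arm, the bias could go the other way.

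What the reply does not meet is the collection gap. A later plan can shorten the cost window, but it cannot supply a ReQoL-10 score that nobody was asked for.

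**Conclusion.** The point holds as an inexpensive improvement, not as an error in a stated analysis. As scheduled, guided versus unguided has no observed utility or self-reported service use after about 6 months from baseline, which leaves 50% to 63% of the time to the 12-month visit uncovered. A cost-utility result for that contrast beyond the 3-month visit would be an extrapolation. Separately, the undefined study period allows a cost window about 2.0 to 2.7 times the utility window; this describes the windows only and says nothing about the size or direction of any bias in the ICER.

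The figures rest on counting the 3-month visit from the end of the course (or taking the stated 6 months) and on the two readings of the 12-month visit. The contrasts with the waitlist and the primary clinical outcomes are not affected by the gap in utilities.

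**What to change.** 1. Add ReQoL-10 and the Use of Care Services questionnaire to the existing 12-month online survey, with EQ-5D-5L for validation, and mark them in the 12-month column of Table 1.
2. State the economic horizon for each contrast. Run guided versus unguided to the 12-month visit, with costs and utilities over the same window.
3. Limit every contrast with the waitlist, for costs and utilities alike, to baseline through the 3-month follow-up.
4. Say whether the 12-month visit is counted from baseline or from the end of treatment, and define the study period for linkage accordingly.

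The cost is a minor ethics amendment and slight extra burden in a survey that participants already complete. Anyone already past the 12-month visit when the change takes effect will have missing 12-month utilities, and the analysis must allow for that. Recruitment is planned to January 2027 (Section 2.1), so the last 12-month visits would fall in 2028; the sooner the forms are added, the fewer participants are lost to this comparison.

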**Significance:**

The results of this trial will provide important data concerning the relative outcomes of these different models of care and will inform the integration of digital psychological interventions translation into healthcare services.

**Ethics and Dissemination:**

The Human Research Ethics Committee of Macquarie University approved the proposed study (Reference No: 520231325151475). The results will be disseminated through peer‐reviewed publication(s).

**ANZCTR Trial Registration Number:**

ACTRN12623001327673.

**Plain Language Summary:**

This study seeks to find out if a 10‐week online psychological treatment can improve the mental health and well‐being of Australian adults with epilepsy. Around 375 participants will be randomly assigned to different groups: one will receive treatment with guidance from mental health clinician (guided group), one without guidance (unguided group), and one starting later (waiting control group). All participants will fill out the same outcome measures online. The main goal of this research is to compare these groups and assess how well the treatment works in improving mental health outcomes.

Key points
Randomized controlled trial comparing two models (guided vs unguided) of delivering a digital psychological intervention, with a control.Adults with epilepsy living in Australia will be recruited.The intervention aims to improve mental health and functional outcomes, with primary outcomes being symptoms of depression and anxiety.The guided model gets the intervention with support from a mental health clinician, the unguided model gets the intervention alone.The comparative efficacy, acceptability, cost‐effectiveness, and long‐term outcomes of these models will be assessed.

## INTRODUCTION

1

Poor mental health is highly prevalent among people with epilepsy (PWE), with one in three estimated to have a lifetime mental health diagnosis.^1^ Comorbid neurological and mental health difficulties can increase healthcare utilization and burden of disease,^2^, ^3^ with poor mental health disrupting the medical management, self‐management, quality of life, morbidity, and prognosis of epilepsy, even when symptoms are mild.^1^, ^4^, ^5^, ^6^ Despite this, there continues to be significant unmet mental health needs of PWE worldwide, prompting recent calls for reform in this area by the World Health Organization.^7^

Despite evidence that psychological treatments can lead to significant improvements in mental health and quality of life for PWE,^8^, ^9^ there are significant barriers that prevent access to such treatments. Highlighting this, a recent survey of epilepsy health professionals found that over 50% were under‐resourced to manage mental health concerns of their patients.^10^ Common barriers to care included a lack of standardized procedures to manage mental health in epilepsy settings and a lack of accessible mental health specialists and interventions.^11^, ^12^ Instead, most PWE within Australia need to arrange their own mental healthcare, and those who try, report significant barriers to accessing effective care, including high out‐of‐pocket costs, travel restrictions, and a lack of specialists and services.^13^ To complicate matters, many PWE report a lack of independence (e.g., lack of driving license) and significant difficulties with their cognitive function (e.g., inattention and poor memory), which can impede their ability to both attend and benefit from traditional face‐to‐face psychological interventions.^4^, ^14^

Digital mental health interventions (i.e., that do not require face‐to‐face contact) are an innovative development that is improving access to psychological care.^15^ These treatments can teach the same core psychological skills as face‐to‐face treatments, such as cognitive restructuring and behavioral activation, but use carefully developed online modules to facilitate learning. Thus, people can engage in these treatments at their own pace, from the convenience of their own home, and potentially at a much lower cost. Digital interventions can also be optimized for cognitive impairment as people can read and revise content as many times as needed. Substantial research supports the efficacy of digital interventions and their clinical equivalence with face‐to‐face psychological care in the general population.^16^, ^17^ There is emerging evidence for the efficacy of digital psychological interventions to improve symptoms of depression and anxiety in adults with neurological disorders including Parkinson's disease,^18^, ^19^ multiple sclerosis (MS),^20^, ^21^, ^22^ migraine,^23^ and epilepsy.^24^, ^25^

Digital mental health interventions can be provided in both guided and unguided models, each with its own potential strengths and weaknesses. In guided models, intervention materials are provided alongside patient‐centered care from a mental health clinician, usually over the phone and/or secure messaging systems. This model of care requires available trained clinicians and their costs to be covered, making the model more expensive and complicated to implement. In unguided models, participants get access to intervention materials but work through the course independently. Unguided models can either involve access to an unguided (or self‐guided) intervention following an initial interview with a clinician or a completely automated intervention with no interview or clinical contact. Research suggests that fully automatic programs experience high dropout rates compared to unguided (with interview) models.^26^ In the context of this research, unguided models refer to those that also include a clinical interview and assessment prior to participation.

Meta‐analytic evidence in the general population, and for those with chronic pain, suggests that on average guided interventions are more clinically efficacious than unguided interventions.^27^, ^28^ In contrast, unguided models have greater public health potential, as they cost less, are easier to implement in routine care settings, and have been found to be efficacious for mild/subthreshold depression.^28^ Yet, participants with severe or complex mental health presentations, such as those with neurological comorbidities including epilepsy, may not achieve good clinical outcomes without clinician support.

Thus, the comparative clinical and cost‐effectiveness of guided and unguided digital interventions remains an important topical area of investigation^15^ and critical information to inform healthcare service providers. Reflecting this, a carefully developed digital chronic pain management intervention was similarly clinically efficacious and acceptable in an unguided and guided model; however, the unguided model was more cost‐effective.^29^ This research highlights the importance of comparative effectiveness trials to inform decision‐makers about the relative merits of different models of care. One recent randomized controlled trial (RCT) in adults with MS compared the efficacy of a digital cognitive behavior‐based program in a guided or unguided format with a treatment‐as‐usual, waitlist, control group.^22^ Both versions of the program led to a significant reduction in depression symptoms compared to the control group. However, a direct comparison between the guided and unguided groups was not performed. To date, there have been two RCTs of digital psychological interventions in epilepsy, both of which utilized unguided models of care.^24^, ^25^ Notably, while both reported that the treatment arms experienced significant improvements in symptoms of depression compared to controls, they also experienced relatively high dropout rates (>25%). On the other hand, an open trial of a guided digital psychological intervention to improve mental health in PWE observed very low rates of attrition (4%).^30^ These findings highlight potential differences in intervention engagement based on levels of guidance. However, conclusions in this area can only be reached following clinical trials that directly compare these different care models.

The aim of the current study is to assess the comparative effectiveness and acceptability of a digitally delivered psychological intervention aimed at improving both mental health (e.g., depression and anxiety) and functional outcomes (e.g., day‐to‐day disability and perceived cognitive function) of Australian adults with epilepsy. Specifically, this three‐armed RCT will directly compare two clinical care models (guided vs. unguided) of delivering an established digital intervention, the Wellbeing Neuro Course, with a treatment‐as‐usual waitlist control (TAU‐WLC) group.

Consistent with previous trials, we hypothesize that:
Both the guided and unguided groups will result in substantial improvements in primary outcomes of depression and anxiety compared to the TAU‐WLC group.There will be non‐inferiority in clinical efficacy between the guided and unguided groups across the primary outcomes.Both the unguided group and guided group will be cost‐effective compared to TAU‐WLC, but the unguided group will be more cost‐effective relative to the guided group due to lower intervention costs.

## METHOD

2

### Registration and ethics

2.1

This is a intervention study conducted at one center: The eCentreClinic, School of Psychological Sciences, Macquarie University, Sydney, Australia. Participants will complete questionnaires at multiple time points. Up to 375 participants will be recruited, with recruitment planned between February 2024 and January 2027.

The project is funded by an NHMRC Medical Research Future Fund grant and additional funding support from Macquarie University. Ethics approval was granted by the Human Research Ethics Committee of Macquarie University (HREC: Reference No: 520231325151475). This trial is registered with the Australian and New Zealand Clinical Trials Registry (ANZCTR; ACTRN12623001327673).

### Study design

2.2

A three‐group CONSORT‐R Compliant RCT design will be employed. Participants will be randomized to:
Immediate guided treatment group (*n* = 150), who receive access to the Wellbeing Neuro Course with clinician support.Immediate unguided treatment group (*n* = 150), who receive access to the Wellbeing Neuro Course without clinician support.TAU‐WLC group (*n* = 75), who will crossover to receive access to the Wellbeing Neuro Course at the 3‐month follow‐up period for groups 1 and 2 (approx. 6 months from baseline). They will have the choice of receiving clinician support or doing the course unguided.

A substudy involving a brief survey of the participants' referring or primary epilepsy health professionals' views on the usefulness of the intervention and care pathway will also be conducted.

